**Methods and analysis:**

This is a single-center randomized controlled study. We plan to recruit adult patients with severe acute pancreatitis from intensive care units for this study. Participants who met the criteria were randomly assigned in a 1:1 ratio, with one group using heparin anticoagulation during continuous renal replacement therapy and the other group using nafamostat mesylate anticoagulation. The primary outcome measure was mean filter life. Secondary outcome measures included changes in Sequential Organ Failure Assessment (SOFA), the Acute Physiology and Chronic Health Evaluation II (APACHE II) score, and inflammatory factors (CRP, PCT, IL-6, IL-8, IL-10, TNF-α) compared with baseline levels on days 1, 3, 5, and 7 after treatment, time to successful initiation of enteral nutrition, blood transfusion requirements, ICU length of stay and total hospitalization days, and follow-up of patients’ blood purification dependency rate and all-cause mortality at 28 days. Safety indicators include the occurrence of any bleeding events (defined by ISTH criteria), filter clotting, and the incidence of heparin-induced thrombocytopenia.

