### Criteria for discontinuing or modifying allocated interventions

If the patient experiences any drug-related safety issues (such as severe bleeding, an unexplained decline in hemoglobin, clinically significant coagulation abnormalities, severe hypotension, or an allergic reaction to the study drug), the use of the assigned anticoagulant will be discontinued or adjusted. If appropriate dose adjustments are made but recurrent circuit coagulation still occurs, or if the attending physician determines that the assigned anticoagulant is no longer appropriate for the patient’s condition, further modification of the intervention will be considered. All changes and their corresponding reasons will be documented.

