### Outcomes

The primary endpoint of this study is the average service life of the CRRT circuit or filter. The functional lifespan of CRRT circuit begins when the extracorporeal circulation of blood starts and ends when the circuit is taken out of service by intensive care unit (ICU) staff (when the treatment goal is achieved, death occurs, or the upper limit of 72 h for filters). The reasons for ICU staff to stop the circuit operation included: (1) the transmembrane pressure on both sides of the circuit exceeded 300 mmHg, (2) visible blood clots hindered the blood flow within the machine, (3) the blood pump could not rotate due to blood clot blockage, (4) other (recorded by the bedside staff). The first three reasons are considered to be cases of circuit clotting. If the bedside staff recorded “other” or the reason for stopping the circuit was missing, adjudication is required. Two senior critical care specialists, who were not involved in the research, independently reviewed these cases and adjudicated the reasons for circuit discontinuation. In case of any disagreement, they resolved it through joint consultation. The outcome of the judgment may be one of three types (coagulated, non-coagulated or unknown condition). The circuit that is selectively discontinued due to reasons during the treatment process (such as transfer within the hospital) is regarded as “non-coagulated.”

The secondary endpoints of this study include: 1. SOFA and APACHE II scores were evaluated on days 1, 3, 5, and 7 after enrollment, and the changes from the baseline (ΔSOFA /ΔAPACHE II) were calculated to reflect the trend of disease progression; 2. Serum levels of pancreatic enzymes (amylase and lipase) and PCT, CRP, IL-6, IL-8, IL-10 and TNF-α were measured on days 1, 3, 5, and 7, and their changes from baseline were analyzed; 3. levels of coagulation parameters(include aPTT, PT, fibrinogen, platelet count) were assessed on specific days (day 1, 3, 5, and 7) together with their changes from baseline values; 4. time to successful initiation of enteral nutrition; 5. blood transfusion requirements(RBC, FFP, platelet units), 6. ICU length of stay and total hospitalization days; 7. Clinical outcomes (blood purification dependency rate, length of ventilator use and all-cause mortality at 28 days).

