Safety outcomes were defined as the occurrence of any adverse events (AEs), including serious adverse events (SAEs) and adverse drug reactions (ADRs), such as the occurrence of any bleeding events (as defined by the International Society on Thrombosis and Haemostasis), allergic reactions, and heparin-induced thrombocytopenia. Researchers are required to continuously monitor for potential adverse reactions throughout the study. In the event of any adverse event, the researchers will promptly take appropriate measures to ensure the safety of the subjects and keep detailed records. For serious adverse events, researchers are required to report the incidents to the ethics committee within 24 h. Study termination will be considered according to the severity and nature of the event.

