### Sample size estimation

The sample size was estimated based on the primary endpoint, which was average service life of the CRRT circuit lifespan or filter (hours). The assumed baseline value of approximately 30 h for the heparin group, together with the standard deviation used in this calculation, were derived from the pooled filter-lifespan data summarized in the network meta-analysis of CRRT anticoagulation strategies by Zhou et al. and the review of circuit-survival determinants by Tsujimoto and Fujii, which indicate that heparin-anticoagulated circuits typically survive on the order of 20–40 h with considerable between-study variability (17, 32). Because the standard deviation of filter lifespan varies significantly across studies, we deliberately chose a relatively conservative value (σ = 8 h) toward the higher end of the reported range, to avoid underestimating the required sample size. A minimum clinically important difference of 4 h (an approximately 13% relative extension over the assumed heparin baseline) was prespecified not purely on statistical grounds but because a gain of this magnitude would be expected to translate into approximately one fewer circuit change per patient over a typical treatment course, with corresponding reductions in nursing workload and blood loss associated with circuit priming and disconnection, as well as lower filter and consumable costs—benefits that are clinically and economically meaningful even though the absolute increase in hours is modest. Assuming a two-sided α level of 0.05 and a power (1–β) of 80%, the sample size was estimated using the approximate formula for comparing the means of two independent samples, resulting in a sample size of approximately 63 cases in each group. Taking into account the approximately 10% dropout rate, it is necessary to recruit 70 participants in each group.

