All participants who received at least one dose of study anticoagulant were included in the safety set. The incidence of adverse events (AEs), serious adverse events (SAEs), and bleeding or coagulation complications were summarized using descriptive statistics and compared between groups with the chi-square test or Fisher’s exact test, as appropriate.

All statistical analyses were performed using SPSS version 26.0 (IBM Corp., Armonk, NY, United States) and R version 4.3.0 (R Foundation for Statistical Computing, Vienna, Austria). A two-sided *p*-value < 0.05 was considered statistically significant.

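### Filter clotting, a recurrent per-circuit event listed as a safety indicator in the abstract, has as its only stated comparison an incidence test that ignores repeat clots and circuit time, or else ignores clustering

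*Protocol article*

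**What the plan says.** - Abstract, Methods and analysis: "Safety indicators include the occurrence of any bleeding events (defined by ISTH criteria), filter clotting, and the incidence of heparin-induced thrombocytopenia".
- Outcomes, safety paragraph: adverse events, serious adverse events and adverse drug reactions, with bleeding, "allergic reactions, and heparin-induced thrombocytopenia" as examples. Filter clotting is not among them.
- Statistical methods, safety analysis: "All participants who received at least one dose of study anticoagulant were included in the safety set". Incidences are then analysed, and "bleeding or coagulation complications were summarized using descriptive statistics and compared between groups with the chi-square test" or Fisher's exact test. Any other categorical variable goes to the same two tests.
- Outcomes, primary endpoint: each circuit has a start, an end and a stop reason. Of the four listed reasons, "The first three reasons are considered to be cases of circuit clotting"; reasons that are missing or recorded as other are adjudicated as coagulated, non-coagulated or unknown.
- Criteria for discontinuing or modifying allocated interventions: the protocol expects that clotting can repeat in one patient ("If appropriate dose adjustments are made but recurrent circuit coagulation still occurs").
- Sample size estimation: the 4 h gain "would be expected to translate into approximately one fewer circuit change per patient over a typical treatment course", so several circuits per patient are foreseen.

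The article gives no clot count, no rate per circuit-hour and no recurrent-event method for clotting. It does not say whether incidence is per patient or per circuit.

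**The concern.** A chi-square or Fisher test needs one independent yes/no per unit. Filter clotting does not supply that in either way of counting.

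- **Per patient**, the natural reading of a participant-based safety set: one clot and six clots score the same, and a patient on CRRT for two days is weighed like one on CRRT for ten.
- **Per circuit**: repeat clots are kept, but circuits within a patient are not independent, so the test's standard error is wrong. The share of circuits that clotted also ignores how long each one ran.

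Two things are at stake. On long courses nearly every patient may have at least one clot, which leaves the comparison little room to show a reduction. If CRRT lasts longer in one arm than in the other, for example because of earlier deaths, the arm with less time at risk will seem to clot less even at the same clotting rate.

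**Working it through.** **Inputs from Sample size estimation:** mean filter life 30 h on heparin, difference 4 h (so 34 h), SD 8 h, two-sided alpha 0.05, power 80%, 63 per arm, 70 after 10% dropout. From Outcomes: "the upper limit of 72 h for filters".

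**Inputs not in the article, assumed and varied:** CRRT course length T, share p of circuits that end in a clot, size of the true reduction, between-patient variation in clotting.

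**1. The plan's own figure.** n = 2 × (1.960 + 0.842)² × 8² / 4² = 62.8, rounded up to 63; 63 / 0.9 = 70. Both reproduce. The article states no power for a clotting comparison.

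**2. Circuits per patient.** With a normal life of mean 30 h and SD 8 h, the chance that a filter reaches 72 h is about 8 × 10⁻⁸, so a course of several days uses several filters. One fewer circuit change requires T/30 − T/34 = 1, so T = 255 h (10.6 days), with 8.5 against 7.5 circuits.

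**3. Patients with any clot at 255 h.** Expected clots are λ = p × T / 30 on heparin and λ × 30/34 in the other arm, taking the clot rate per hour to fall in line with filter life. The proportion with any clot is 1 − exp(−λ).
- p = 30%: λ = 2.55 and 2.25, giving 92.2% and 89.5%, a gap of 2.7 points.
- p = 70%: λ = 5.95 and 5.25, giving 99.74% and 99.48%, a gap of 0.26 points.

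Chi-square power at 63 per arm is 4-8%. These proportions give every patient the same clot rate. With a gamma frailty of variance 0.5 (assumed), the proportion is 1 − (1 + 0.5λ)⁻²: on heparin 81% at λ = 2.55 and 94% at λ = 5.95. The ceiling is then softer.

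**4. Short courses.** At 48 h and p = 30%, λ = 0.48 gives 38%. At 72 h and p = 50%, λ = 1.2 gives 70%. There is no ceiling.

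**5. Unequal exposure.** Give both arms the same clot rate (p = 50%, 30 h circuits). A 72 h course gives 1 − exp(−1.2) = 70% with any clot; a 48 h course gives 1 − exp(−0.8) = 55%. The 15-point difference comes from time on CRRT alone.

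**6. Power against a rate analysis**, 63 per arm, for an assumed 30% lower clot rate. The standard error of the log rate ratio is √[(1/λ₁ + k)/63 + (1/λ₂ + k)/63], with k = 0.5 (overdispersed) or k = 0 (Poisson).

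| Course, clot share | Any clot, heparin vs other arm | Chi-square on any clot | Rate, overdispersed to Poisson |
|---|---|---|---|
| 72 h, 30% | 51% vs 40% | 26% | 27-34% |
| 120 h, 50% | 87% vs 75% | 35% | 48-73% |
| 168 h, 70% | 98% vs 94% | 24% | 60-95% |
| 255 h, 50% | 99% vs 95% | 21% | 62-96% |
| 255 h, 90% | 100% vs 99.5% | 7% | 69-100% |

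The any-clot columns assume no between-patient variation.

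For the 4 h effect alone the rate analysis is weak too. At 255 h (p = 30-90%) its power is 11-14% overdispersed or 19-47% Poisson; at 48-72 h (p = 30-50%) it is 6-9% or 7-11%. For a halved clot rate the any-clot test keeps 81-86% power at 120 h with p = 50% and at 72 h with p = 50-90%, but falls to 21% at 255 h with p = 90%.

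**The case against.** The strongest reply has four parts.

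1. **The target is inferred.** The safety analysis speaks of coagulation complications, which could mean patient-level disturbances of coagulation, and the body's safety definition does not name filter clotting. This stands in part: the link rests on the abstract. But if filter clotting is a safety indicator, no other stated safety method fits it, and the general rule for categorical variables leads to the same tests.
2. **The unit is inferred.** The article never says that clots collapse to one yes/no per patient, and such detail may sit in an unseen analysis plan. True, but a test is stated, and it does not suit the event under either unit.
3. **Clotting is already analysed on a time scale**, through filter life with Kaplan-Meier, log-rank and Cox analyses. This stands and limits the harm. It does not fully replace a clotting comparison: filter life also ends at treatment goal, death or the 72 h limit, and the methods do not say that clotting is the event.
4. **The damage can be overstated.** A reader might infer that both arms must approach 100%, that a real reduction will be reported as no difference, or that a rate analysis would have near-certain power. The documents support none of these. They give neither course length nor clot share, short courses show no ceiling, a large reduction can stay detectable, and near-certain power for the 4 h effect arises only if between-patient variation is left out.

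**Conclusion.** The point holds in a limited form. The stated incidence test does not fit a recurrent, exposure-dependent event. Per patient it drops repeat clots and time at risk; per circuit it ignores clustering. On the 255 h course implied by the protocol's own expectation, about 92-99.7% of heparin patients would have a clot if 30-70% of circuits clot at a rate common to all patients, so a real reduction may be missed. On 48-72 h courses with 30-50% clotting the figure is 38-70%; the remaining fault there is sensitivity to unequal time on CRRT. A rate analysis uses more of the data, but its gain depends on course length, clot share and between-patient variation, and high power for a 4 h effect is not assured.

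A non-significant any-clot percentage would not contradict a positive result on filter life, because it answers a different question. The sample size, the primary conclusion and the safety review triggers under Interim analyses do not rest on this comparison.

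**What to change.** 1. Make the abstract and the safety paragraph under Outcomes agree on whether filter clotting is a safety outcome.
2. If it is, take it out of the chi-square/Fisher list in the safety analysis. Define the event as a circuit stopped for any of the first three listed reasons or adjudicated as coagulated, and report events per 100 circuit-hours by arm.
3. Compare the arms with a Poisson or negative binomial model on counts per patient, with log(circuit-hours) as offset and robust standard errors.
4. Keep the percentage of patients with at least one clot as a descriptive line.

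The cost is a few sentences, one extra model and a measure less familiar to readers than a percentage. No new data are needed, since circuit times and stop reasons are already recorded for the primary endpoint.

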#### Interim analyses

No formal interim analysis of treatment efficacy is planned, given the short treatment and follow-up duration of this trial. However, independent of any efficacy assessment, a pre-specified safety stopping rule has been established. The DMC will conduct an ad hoc safety review whenever any of the following occurs in either study arm: (1) the incidence of major bleeding (defined by ISTH criteria) reaches or exceeds 20% of enrolled participants in that arm; (2) two or more cases of heparin-induced thrombocytopenia (in the UFH arm) or two or more cases of severe anaphylactoid/hyperkalemic reactions attributable to nafamostat mesylate (in the NM arm) are reported; or (3) any single adverse event is judged by the treating physician and confirmed by the DMC to be directly and probably related to the study anticoagulant and life-threatening. Upon triggering any of these thresholds, the DMC will unblind and review the relevant safety data and may recommend continuation without modification, protocol amendment (e.g., dose adjustment or revised monitoring), or early termination of the trial to the trial steering committee. These numerical thresholds will be reviewed and, if necessary, refined by the DMC biostatistician prior to trial initiation.

#### Methods for additional analyses (e.g., subgroup analyses)

Subgroup analyses will assess whether treatment effects differ across predefined etiologies of acute pancreatitis (biliary, alcoholic, hypertriglyceridemia-related, post-ERCP, and other). Adjusted analyses will be performed using multivariable regression models to control for potential confounding factors.

#### Methods in analysis to handle protocol non-adherence and any statistical methods to handle missing data

Because of the prospective design and short follow-up period of this trial, the occurrence of missing data in this study will be rare. Protocol deviations will be incorporated within an intention-to-treat framework, supported by a per-protocol analysis, while missing data will be handled primarily with mixed-effects models and, when necessary, multiple imputation with sensitivity checks.

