## Introduction

### Background and rationale

Severe acute pancreatitis (SAP) is a common type of critical abdominal condition in clinical practice. Due to its rapid progression, SAP frequently prone to cause multiple organ dysfunction or even failure, resulting in high complication and mortality rates (1, 2). In patients with SAP who develop persistent organ failure, the mortality rate can be as high as 40% (3–5). Due to the changes in the body functions and circulation of patients with severe acute pancreatitis, the levels of inflammatory factors in their bodies will show a significant upward trend, thereby triggering a cascading reaction of inflammatory factors and subsequently leading to multiple organ dysfunction (6, 7). Previous studies (1, 6–8) have shown that in the early phase of SAP, the excessive release of inflammatory factors will further aggravate the severity of systemic inflammatory response syndrome and promotes the development of infected pancreatic necrosis. Therefore, inflammatory factors are significant factors influencing the onset and treatment of patients with SAP, and they are also important indicators reflecting the condition of patients with SAP (1, 9, 10).

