### Eligibility criteria

Participants will be considered for inclusion in the study if they meet the following criteria upon admission to the ICU or during stay in the ICU: (1) adults over 18 years old, (2) diagnosed with severe acute pancreatitis (SAP) according to the revised Atlanta classification (2012), meeting at least one of the following: Persistent organ failure ( > 48 h), or APACHE II score ≥ 8 or SOFA score ≥ 4 at ICU admission, (3) requiring blood purification therapy [continuous renal replacement therapy (CRRT)] due to systemic inflammatory response, acute kidney injury, or hypercytokinemia, (4) informed consent obtained from patient or surrogate.

The exclusion criteria for participants included the following: (1) known hypersensitivity or contraindication to NM or UFH, (2) severe coagulation disorders (INR > 2.0), active major bleeding (such as intracranial hemorrhage, ongoing gastrointestinal bleeding) or recent uncontrolled bleeding and bleeding diseases or platelet count < 30 × 10^9^/L, (3) severe hepatic failure (Child–Pugh C), (4) History of heparin-induced thrombocytopenia (HIT), (5) pregnancy or lactation. (6) Chronic kidney disease requiring dialysis before ICU admission, (7) expected survival < 48 h or refusal to participate.

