### Statistical methods

#### Statistical methods for primary and secondary outcomes

Continuous variables were tested for normality using the Kolmogorov–Smirnov test. Normally distributed data were presented as mean ± standard deviation (SD) and compared using the independent-samples *t*-test. Non-normally distributed variables were reported as median (interquartile range, IQR) and analyzed using the Mann–Whitney U test. Categorical variables were expressed as counts (percentages) and compared using the χ^2^ test or Fisher’s exact test, as appropriate.

In addition, the primary endpoint of this study was the mean lifespan of the hemodialysis filter during CRRT. Kaplan–Meier survival analysis was conducted to compare the cumulative probability of filter life over time, with the log-rank test applied for group comparison. To control for potential confounders (e.g., disease severity scores), multivariable linear regression and Cox proportional hazards models were used as sensitivity analyses.

Secondary outcomes included the changes in disease severity scores (SOFA and APACHE II), pancreatic enzymes (amylase, lipase) and inflammatory biomarkers (PCT, CRP, IL-6, IL-10, TNF-α) measured on Day 1 (baseline), day 3, day 5, and day 7 after randomization. To evaluate time-dependent trends and group differences, a repeated-measures analysis of variance (RM-ANOVA) was applied for normally distributed variables. Baseline disease severity characteristics, including etiology, CTSI/EPIC radiological scores, and the presence and grade of intra-abdominal hypertension, will be summarized descriptively and compared between groups using the χ^2^ test, Fisher’s exact test, or the Mann–Whitney U test, as appropriate. The assumption of sphericity was tested by Mauchly’s test, and when violated, the Greenhouse–Geisser correction was used to adjust degrees of freedom. Differences in change-from-baseline values (ΔSOFA, ΔAPACHE II, and Δbiomarker levels) between groups were analyzed using the independent-samples *t*-test or Mann–Whitney U test, as appropriate. Correlations between the changes in inflammatory markers and changes in severity scores were assessed using Spearman’s rank correlation coefficient.

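### The missing-data rule does not separate values missing in living patients from day 3–7 SOFA, APACHE II and marker values that do not exist because the patient died, and the change-score tests drop those patients

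*Protocol article*

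**What the plan says.** The section on non-adherence and missing data states that "the occurrence of missing data in this study will be rare", giving the prospective design and short follow-up as reasons. It then sets one rule: "missing data will be handled primarily with mixed-effects models and, when necessary, multiple imputation with sensitivity checks". Death is not mentioned there.

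The Outcomes section lists among the secondary endpoints that "SOFA and APACHE II scores were evaluated on days 1, 3, 5, and 7 after enrollment", analysed as change from baseline to show the trend of disease progression. Enzymes and inflammatory markers follow the same days. All-cause mortality at 28 days is a separate secondary outcome.

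The section on statistical methods for primary and secondary outcomes names a repeated-measures ANOVA and adds: "Differences in change-from-baseline values (ΔSOFA, ΔAPACHE II, and Δbiomarker levels) between groups were analyzed using the independent-samples" t-test or the Mann–Whitney test. It gives no rule for a patient who died before the assessment.

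On how often that may happen, the Background says: "In patients with SAP who develop persistent organ failure, the mortality rate can be as high as 40" per cent, without a time horizon. The eligibility criteria admit patients with "Persistent organ failure ( > 48 h), or APACHE II score ≥ 8 or SOFA score ≥ 4 at ICU admission" and exclude those with "expected survival < 48 h or refusal to participate".

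**The concern.** A SOFA score on day 5 or 7 has no value for a patient who died on day 4. That differs from a score that exists but was not recorded, and the two call for different handling. The plan puts both under one rule.

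The two analysis sections also lead to different quantities. A t-test or Mann–Whitney test on change scores uses only patients alive at the visit, and a repeated-measures ANOVA in its usual form needs every visit. A mixed model fitted under missing at random implicitly carries a dead patient's course forward as if the patient had lived; multiple imputation would do so literally. In neither case does death count as the worst course, although the score is meant to show progression.

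If one arm keeps more of its sickest patients alive, their high scores stay in that arm's average and the arm can look worse on ΔSOFA and ΔAPACHE II. The Discussion relies on these scores and markers to explain what nafamostat does beyond anticoagulation, so a misread comparison would matter there.

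**Working it through.** **Inputs from the protocol.** 70 patients per arm, 140 in all (Sample size estimation). Assessments on days 3, 5 and 7 against a day-1 baseline (Outcomes, Table 1). Mortality up to 40% with persistent organ failure, no horizon (Background).

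**Not in the protocol, so assumed.** 28-day mortality in this trial, the timing of deaths, and the distribution of SOFA and its link with death.

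**1. The plan's own figure.** The missing-data section gives none. The sample size reproduces: n = 2 × [8 × (1.960 + 0.842) / 4]² = 62.8, so 63 per arm; 63 / 0.90 = 70. It concerns filter life and is not in question.

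**2. How many values death could remove.** With 28-day mortality m and a constant hazard, the number without a day-d value is 140 × [1 − (1 − m)^(d/28)]. If half of the 28-day deaths fall by day 7, it is 140 × m × 0.5.

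| Assumed 28-day mortality | Day 7, constant hazard | Day 7, half of deaths by then |
|---|---|---|
| 10% | 140 × (1 − 0.90^0.25) = 3.6 (about 3%) | 7 (5%) |
| 20% | 140 × (1 − 0.80^0.25) = 7.6 (5%) | 14 (10%) |
| 40% | 140 × (1 − 0.60^0.25) = 16.8 (12%) | 28 (20%) |

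At 40% and constant hazard, about 7.5 patients lack a day-3 value and about 12 a day-5 value.

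**3. What this can do to ΔSOFA.** Simulation with 70 per arm and 2,000 runs. Baseline SOFA is normal (mean 10, SD 3). The latent change to day 7 is normal (mean −3, SD 3) and the same in both arms. Death by day 7 is logistic in the latent day-7 score, with slope 0.3, 0.6 or 1.0 per point, calibrated to the stated mortality. Two analyses were compared: a t-test in survivors, as the change-score tests would give, and a missing-at-random fill (change regressed on baseline within arm, prediction used for the dead) as a stand-in for the mixed-model or imputation route. A positive gap means that the arm with fewer deaths looks worse.

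| Day-7 mortality | Gap, survivors only | Gap, missing-at-random fill | Survivors-only tests with p < 0.05 |
|---|---|---|---|
| 15% v 15% | about 0 | about 0 | 4–5% |
| 10% v 5% | 0.1–0.2 | 0.1–0.2 | 5–7% |
| 20% v 10% | 0.2–0.3 | 0.2–0.4 | 7–9% |
| 30% v 15% | 0.3–0.4 | 0.3–0.6 | 8–14% |

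In the 30% v 15% case more than nine in ten of the significant results point the wrong way. Filling in does not repair the comparison; under these assumptions it widens the gap.

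**4. Sensitivity to the assumptions.** A second simulation (300 repeats, baseline SOFA mean 8) let death depend on the observed day-3 score. At 20% v 10% the gap was about +0.03 points in survivors and −0.02 with the fill, so effectively none. Here the estimate is not visibly biased, but a doubling of deaths leaves no trace in it.

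**The case against.** A reader might infer that the plan orders scores to be filled in for dead patients. It does not say so. It names a general rule and is silent on death; the consequence follows only because no exception is made. The article is condensed and an analysis plan may exist that makes the distinction. That limits the point to what the printed rule says, but that rule covers all missing data and, applied as written, gives no way to treat death differently.

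A reader might also infer that mortality disproves the statement on rarity. It does not: if post-death values are not missing data, deaths cannot contradict it. The retention section supports the narrow reading, with ICU care, routine assessments and low expected loss. The 10% dropout allowance is a planning margin for the filter-life sample size, not a forecast of absent scores. What stands is that the statement leaves open whether deaths are included.

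The 40% figure applies to persistent organ failure, and patients can also qualify on APACHE II or SOFA alone. Nothing in the protocol assumes a twofold mortality difference between two anticoagulants, and at equal mortality the gap vanishes. Mortality is reported in its own right, so deaths are not hidden. Finally, ranking death worst is one choice of estimand among several. All of this stands and keeps the size of the point modest.

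**Conclusion.** The point holds as a gap in how the secondary analyses are specified. Neither the missing-data rule nor the change-score tests say what happens to a patient who dies before day 3, 5 or 7, and the two lead to different comparisons, both blind to death.

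Perhaps 5–20% of day-7 values could be absent through death if 28-day mortality is 20–40%, and about 3% at 10% mortality with a constant hazard. If mortality differs between arms and death follows the unobserved score, ΔSOFA can favour the arm with more deaths by about 0.2–0.4 points at 20% v 10% day-7 mortality and 0.3–0.6 at 30% v 15%. The inflation of false-positive results is modest. All of these inputs are assumptions, and another plausible model gave almost no gap, so they show what can happen and are not a forecast.

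Only secondary endpoints are touched. For the primary endpoint the Outcomes section names death as an end of circuit life. The change is worth making before analysis but is not critical to the trial's main conclusion.

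**What to change.** In the missing-data section:

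- Limit mixed models and multiple imputation to values missing while the patient is alive, and state that nothing is imputed after death.
- Reword the statement on rarity so that it refers only to values missing in living patients and does not cover deaths.

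In the statistical methods section:

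- For ΔSOFA and ΔAPACHE II at days 3, 5 and 7, add a rank-based comparison in which death before the assessment ranks worst, earlier death worse than later.
- Show the survivors-only change beside it, with deaths and numbers alive per arm at each visit.
- Report the markers while alive, with the same counts.

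The cost is wording and a few extra table rows. Sample size and data collection do not change. The downside is small: the ranked score mixes death with organ function, which is why the survivors-only result stays beside it. If the sponsor prefers another estimand, such as a joint model with survival, that is acceptable provided that it is named in advance and treats death explicitly.
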